**Descriptive tables as shown below will be populated:**

| **Baseline characteristics** |
| --- |
| Age (years), mean (SD, range) |
| Serum PSA (ng/ml), mean (SD, range) |
| Race |
| Reason for PSA test and Biopsy, % (n)  PSA screening (patient request)  Lower urinary tract symptoms |
| Prostate Volume (mL), mean (SD, range) |
| PSA Density (ng/mL^2^), mean (SD, range) |
| Grade group score on MRI-TB, % (N)  3+4  4+3 |
| MRI-TB, mean (SD, range)  Total Cores  Total Positive Cores  % Positive Cores |
| Risk category (%, n)  Unfavorable intermediate-risk |

| **Peri-operative characteristics** |
| --- |
| Procedure time (minutes), mean (SD, range) |
| Procedure type: HIFU or Cryoablation |
| Discharge time from procedure end (hours), mean (SD, range) |
| Length of catheterization (days), mean (SD, range) # |
| Dysuria (negative urine culture), % (n)  Duration (days), mean (SD, range) |
| Intermittent hematuria (start of stream only), % (n)  Duration (days), mean (SD, range) |
| Urinary debris, % (n)  Duration (days), mean (SD, range) |
| Urinary tract infection (positive urine culture) (%, n) |
| Stricture (%, n) |
| Recto-urethral fistula (%, n) |

| **Histological characteristics at 12-months MRI-TB** |
| --- |
| Number of cores taken, mean (SD, range) |
| PSA density (ng/mL^2^), mean (SD, range) |
| Absence of any cancer (%, n) |
| Absence of Gleason pattern 4 (%, n) |

The primary objective will be expressed as proportions of total number of patients and the 95% confidence interval of the proportion will be presented. Number and grade of complications will be reported.

HrQOL measures collected at 6- and 12-months will be compared to baseline measures using paired tests. In addition, the 6-month and 12-month change from baseline will also be tabulated

PSA: The mean PSA levels at each visit, the overall percent reduction in PSA levels from baseline to each visit, and the proportion of subjects with a PSA reduction compared to baseline at each visit will be presented. Mean PSA nadir and post-nadir PSA values through 12-months post-treatment will be summarized.

Testosterone recovery: Number of men who have recovered normal serum testosterone levels will be expressed as proportions of total number of eugonadal patients and the 95% confidence interval of the proportion will be presented.

Secondary or Adjuvant Treatment: The number and proportion of subjects undergoing secondary treatment during the study will be presented.

# SAFETY EVENT AND PRODUCT QUALITY COMPLAINTS REPORTING – PRINCIPAL INVESTIGATOR RESPONSIBILITIES

## Health Authority

As the Principal Investigator of the study and to the extent required by any applicable laws or regulations in each country/territory, the Institution/Investigator (University of Chicago/PI) shall be responsible for complying, within the required timelines, with any safety reporting obligation towards the competent health authorities, the Ethics Committees (EC) or Independent Review Board (IRB) and the participating (co- or sub-) investigators.

## General

Training: Institution/Sponsor of the Study shall be responsible for training the Study personnel (including the Investigator) on managing safety information arising from the Study according to agreed procedures and the requirements of this Agreement.

Maintenance of Safety Information: All safety data arising from the Study shall be maintained in a clinical database in a retrievable format. The Institution and Investigator shall provide a summary of all non-serious adverse events (NSAES) annually, and both serious and non-serious adverse events will be summarized in the final Study report.

## Adverse Event (AE) Definitions

- - 1. Adverse Events

An adverse event is any untoward medical occurrence in a patient or clinical investigation subject administered a pharmaceutical product that does not necessarily have a causal relationship with the treatment. An adverse event can be any unfavorable and unintended sign (including a laboratory finding), symptom or disease temporally associated with the use of a medicinal (investigational) product, whether or not related to the medicinal (investigational) product.

At each evaluation patients should be interviewed in a non-directed manner to elicit potential adverse reactions from the patient. The occurrence of an adverse event will be based on changes in the patient’s physical examination, laboratory results, and/or signs and symptoms, and review of the patient’s own record of adverse events.

Adverse events will be followed until resolution while the patient remains on-study. Once the patient is removed from the study, events thought to be related to the study medication will be followed until resolution or stabilization of the adverse event, or until the patient starts a new treatment regimen, or death, whichever comes first. Subjects will be followed for AEs/SAEs for 30 days after their last dose of study drugs.

- - 1. Unexpected Events

Unexpected events are those not listed at the observed specificity or severity in the protocol, informed consent, investigator brochure, or FDA-approved package insert. An event is considered unexpected if it is listed as occurring within the class of drugs or otherwise expected from the drug’s pharmacological properties but has not been previously observed with this specific investigational agent.

- - 1. Adverse Reactions

An adverse event is considered to be an adverse reaction if there is evidence to suggest a causal relationship to the study agent. This may include a single occurrence of an event strongly associated with drug exposure (e.g. Stevens-Johnson Syndrome), one or more occurrence of an event otherwise uncommon in the study population, or an aggregate analysis of specific events occurring at greater than expected frequency.

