## Post-Focal Therapy Treatment Efficacy/Surveillance mpMRI and MRI-TB

At 12-months from the time of FT, a SOC mpMRI and MRI-TB will be performed to determine treatment response. Both the imaging study and prostate biopsy results will be used to measure efficacy of the proposed combination treatment. However, if a patient has any other post-treatment biopsy results these may also be used to assess for post-treatment efficacy even if not performed with an mpMRI guided biopsy.

Specifically, an MRI-TB will sample the ablated and unablated prostate tissue to determine if residual CSPCa (GG ≥2) remains in the treated and/or untreated prostate tissue. The mpMRI used for the MRI-TB will follow the same imaging protocol as the pre-treatment study and reported in the same manner. Documentation of the biopsy site(s) will be required. If a new suspicious radiographic lesion(s) is/are detected on the subject’s 12-month mpMRI which was/were not present in the pre-treatment [screening] mpMRI then the targeted biopsy cores of the suspicious area(s) will be obtained. Otherwise, if no suspicious lesions are noted in the 12-month mpMRI then random biopsies from the unablated prostate tissue will be obtained per SOC during the MRI-TB.

- Two 18-gauge biopsy cores will be collected from the ablated area(s) and one each from periablation zone and untreated prostate for biobanking and exploratory outcomes on correlatives.

If the 12-month MRI-TB identifies the presence of CSPCa in the ablated or unablated prostate tissue then the patient will be offered a second treatment with FT (if eligible for such treatments) and the follow-up visits for the re-treatment will be the same as the primary treatment. The patients will stay in the study and will continue to be followed up until 12-months from the first FT procedure. For patients with residual/recurrent cancer who decline or are ineligible for a second FT procedure, one of the whole gland treatments, either radical prostatectomy, whole gland ablation or radiation therapy, will be offered. These data will be recorded as part of report of secondary outcomes. Patients who choose to undergo whole gland treatment during the study follow-up will exit the study at this point. HRQOL surveys, PSA and testosterone levels will be obtained at the exit.

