## Duration of Follow-Up

Subjects will be followed for survival and recurrence for up to 1-year from the date of their FT procedure. Subjects removed from study for unacceptable AE(s) will be followed until resolution or stabilization of the AE.

Refer to the study calendar (section 15) for the timing and frequency of the following activities in follow-up. Subjects in the post-op follow-up phase should be seen in clinic to collect PSA levels (per clinical SOC) and assess for survival and recurrence until death, withdrawal of consent, becoming lost to follow-up or at the end of the study (up to 1-year after FT procedure), whichever occurs first. HrQOLs (I-PSS, SHIM and the EPIC-26) will also be completed at designated follow-up visits. Subjects may also have a focused abdominal and pelvic genitourinary examination in follow-up if clinically indicated.

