# STATISTICAL CONSIDERATIONS

## Study Design/Endpoints

This study will be a multi-institutional single arm phase I/II trial with a recruitment goal of 57 patients with treatment naïve non-metastatic intermediate-risk PCa.

Primary endpoints

1. To determine the proportion of men with CSPCa (GG ≥2) in the ablated prostate tissue by performing a surveillance mpMRI and MRI-TB at 12-months following FT.
2. To determine the proportion of men with CSPCa (GG ≥2) in the unablated prostate tissue by performing a surveillance mpMRI and MRI-TB at 12-months following FT.
3. To demonstrate the safety of combining ADT, and FT for the treatment of men with histopathologic diagnosis of GG 2 & 3 PCa, with PSA level < 20 ng/mL utilizing the NCI’s CTCAE v.5 classification to quantify and characterize the incidence of AEs.

Secondary endpoints

1. To define change in genitourinary and sexual function from baseline following ADT, and FT by measuring the subject’s HRQoL (I-PSS, SHIM, EPIC-26) at 6-and 12-months after FT.
2. To determine the PSA response to the combination treatment by measuring the subject’s PSA at “baseline” (PSA at time of initial diagnosis) and then at 3-months, 6-months, and 1-year from FT.
3. To determine the proportion of men converting to whole gland therapy (radical prostatectomy or radiation therapy) and/or requiring systemic therapy and/or developing metastases and/or dying of PCa during the course of study.
4. To determine the proportion of men without any PCa on any post treatment prostate biopsy.
5. To determine the proportion of men with normal baseline serum testosterone who had testosterone recovery (defined as testosterone levels >300 ng/dL) at 6-, 9- and 12-months after FT.

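### Protocol Section 14.3 ties adverse-reaction status and post-removal follow-up to the drug alone, so an ablation injury has no related category and, at some exits, no follow-up rule

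*Protocol*

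**What the plan says.** Primary endpoint 3 (Protocol, Study Design/Endpoints) begins "To demonstrate the safety of combining ADT, and FT" and is to be measured by the incidence of adverse events under CTCAE v.5. The second primary objective likewise concerns the combination.

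Adverse Event (AE) Definitions (Section 14.3) sets four rules that matter here.

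- The basic definition mentions a drug but demands no causal link to it: "any untoward medical occurrence in a patient or clinical investigation subject administered a pharmaceutical product that does not necessarily have a causal relationship".
- While a man is on study, his adverse events of any cause are followed to resolution.
- After removal the scope narrows: "Once the patient is removed from the study, events thought to be related to the study medication will be followed until resolution or stabilization". That follow-up ends earlier if a new treatment regimen starts or the man dies.
- On causality: "An adverse event is considered to be an adverse reaction if there is evidence to suggest a causal relationship to the study agent".

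Three other sections govern men who leave.

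- Duration of Follow-Up (10.2): "Subjects removed from study for unacceptable AE(s) will be followed until resolution or stabilization of the AE".
- Withdrawal of Consent (10.4): the PI or treating physician goes on following adverse events outside the study. The same section sends events present at discontinuation or withdrawal back to Section 14.
- Post-Focal Therapy Treatment Efficacy/Surveillance: "Patients who choose to undergo whole gland treatment during the study follow-up will exit the study at this point". Quality-of-life surveys, PSA and testosterone are listed for that exit. An adverse event assessment is not.

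**The concern.** The trial tests a drug plus a procedure, but the rules on causality and on follow-up after removal recognise only the drug. The protocol itself foresees procedural harm: the background mentions genitourinary fistula, and the peri-operative table has rows for stricture and recto-urethral fistula. As worded, a fistula that the surgeon attributes to the ablation has no route to being an adverse reaction.

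Two parts of the safety record are at stake: attribution of events to the procedure, and the outcome of procedural injuries still open when a man leaves. Men who convert to whole-gland treatment matter most here, because they leave at a point where no adverse event assessment is named.

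**Working it through.** The point is one of wording, so there is no planned figure to reproduce. The check sets the rules side by side.

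**Step 1. Does an ablation injury count as an adverse event?** Yes. The definition requires that the man was given a pharmaceutical product, not that the product caused the event. ADT starts 8 to 12 weeks before FT (Focal Therapy Procedure section), and the primary safety population consists of men who received both (Analysis of Primary and Secondary Endpoints). So every ablated man meets the condition.

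**Step 2. Can it be classed as treatment-related?** Not through FT. The only causal category requires that "there is evidence to suggest a causal relationship to the study agent", and no parallel category exists for the procedure.

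**Step 3. Is an unresolved FT-related event followed?**

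| Situation | Governing text | FT-related event covered? |
|---|---|---|
| On study | 14.3: any cause, to resolution | Yes |
| Removed for an unacceptable adverse event | 10.2: not limited to the drug; 14.3: drug-related only | Yes under 10.2, not under 14.3 |
| Consent withdrawn | 10.4: continues outside the study, but also refers back to Section 14 | Yes on the first sentence; unclear after the referral |
| Exit to whole-gland treatment | Post-FT surveillance section: no adverse event assessment named; 14.3: drug-related only | No |
| Removed to receive a prohibited anticancer treatment (General Concomitant Medication section) | 14.3 only | No |
| Completes 12 months | 14.3 speaks of removal; a completer is not clearly removed | No rule clearly applies |

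**Step 4. What does the new-regimen cut-off do?** Prostatectomy or radiation is naturally read as a new treatment regimen. For a man leaving for either, follow-up under 14.3 would end for drug-related events too. Adding FT to the wording would therefore not close the gap at this exit unless the cut-off is also settled.

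**Step 5. Does other data collection fill the gap?** Only in part. Calendar footnote 10 gathers unspecified post-surgical data to one year after FT, and the questionnaires track urinary and sexual function. Neither assigns a cause to an event or follows it to its end.

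**The case against.** The strongest reply is that the reported safety result does not depend on these rules. The endpoint is the incidence of adverse events, the analysis section reports number and grade of complications, and no analysis by relatedness is specified. All serious events go to the cancer center whatever their cause (Adverse Event Reporting Requirements). Stricture, fistula, infection and hematuria are tabulated without a causal test. I-PSS and SHIM are scheduled at 30 days and at 3, 6, 9 and 12 months after FT, EPIC-26 at 3, 6 and 12 months, and surveys are repeated at whole-gland exit. FT is also described as a clinical procedure that research does not alter.

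Most of this stands, and it rules out four stronger readings.

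- *Ablation injuries are not adverse events, or are simply dropped at exit.* Step 1 answers the first part. Sections 10.2 and 10.4 answer much of the second.
- *The trial would report safety for ADT only.* Incidence and grade are reported whatever the cause.
- *ADT events are followed after whole-gland exit while FT events are not.* The new-regimen cut-off plausibly ends both.
- *The background rates of erectile dysfunction and incontinence, applied to 57 men, give the size of the loss.* Those rates cover any such event across case series with 9 to 70 months of follow-up, not events still open at exit. An investigator might also relate erectile dysfunction to ADT.

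The description of FT as standard care does not rescue the wording. The protocol chose the safety of the combination as a primary endpoint, so its causality and follow-up rules should reach both components.

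**Conclusion.** The point holds in a limited form. Section 14.3 confines adverse-reaction status and post-removal follow-up to the drug, while Sections 10.2 and 10.4 are not so confined. The result is no related category for an ablation injury in any treated man, and no stated follow-up requirement for an unresolved FT-related event at exits other than removal for an adverse event or withdrawal of consent.

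The count of adverse events by incidence and grade is not undermined by this wording; attribution and final outcome are. The number of men affected cannot be derived from the documents, which give neither an expected conversion rate to whole-gland treatment nor a rate of events unresolved at exit.

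The conclusion assumes that *study medication* and *study agent* mean ADT, and that the calendar's collection period, to 30 days after FT, governs which events are recorded. Section 14.3 also says "Subjects will be followed for AEs/SAEs for 30 days after their last dose of study drugs". Read literally for one injection on day 0, that period ends on day 30, before FT on days 56 to 84 (56 − 30 = 26 to 84 − 30 = 54 days earlier). That conflict over the collection window is a separate matter, and this point does not rest on it.

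The defect is worth correcting because it touches a primary endpoint and the correction is cheap.

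**What to change.** 1. In Section 14.3, replace *study medication* and *study agent* with *study treatment (ADT and/or the FT procedure)*.
2. On the adverse event form, record relatedness to ADT and to FT separately.
3. Reconcile Sections 10.2, 10.4 and 14.3 and the whole-gland exit text in the post-FT surveillance section, including the new-regimen cut-off. One stated rule should cover unresolved events related to either component at every type of exit, completion at 12 months included.

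The cost is amendment wording, an added relatedness field, and follow-up through clinic records for what should be a few men. Sample size, visits and the primary analysis are unaffected.

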## Pharmacological Treatments: Androgen Deprivation Therapy

Pharmacologic research treatment will be administered on an outpatient basis. No investigational or commercial agents or therapies other than those described below may be administered with the intent to treat the subject’s malignancy.

Subjects will initiate ADT via any generic luteinizing hormone-releasing hormone agonist such as leuprolide acetate 22.5 mg subcutaneous 3-month injection once at baseline for a total of 3-months of treatment. ADT will be dosed to complete 3-months of pharmacologic treatment per study protocol. Of note, each participant will complete at least 8-weeks of neoadjuvant treatment prior to FT.

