## Focal Therapy Procedure Combination with Androgen Deprivation therapy

Partial ablation of the prostate, although not considered to be standard among the intermediate- to risk PCa population, is a PCa management option for men interested in undergoing this treatment modality following the shared decision-making process with a urologist. Importantly, the description of the FT procedure that follows does not differ from partial ablation of the prostate provided for PCa patients as part of clinical care and is not considered in and of itself to be altered or changed in any way for research purposes.

Within 8- to 12-weeks of initiation of ADT, FT will be performed. The volume of tissue treated will be determined based on the discretion of the treating investigator, and as indicated according to the subject’s MRI-TB results at the time of his PCa diagnosis.

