# STUDY CALENDAR

| **Visit number** | **1** | **2** | **3** | **4** | **5** | **6** | **7** | **8** | **9** |
| --- | --- | --- | --- | --- | --- | --- | --- | --- | --- |
| **Study milestones** | Screen | Drug Start | 8 wk mpMRI | FT | 30-Day EOT | 3 mo post-op | 6 mon  Post op | 9 mo  Post op | 1-year post-op  MRI-TB |
| **Time-point** | -28 days |  | 8 wks post V2 | 8-12 wks from V2 | 30-days post-FT | 3 mo post FT | 6mon-post-FT | 9 mo post FT | 1-year post-FT |
| **Windows** |  |  | +/- 7 days | +/-7 Days | +/- 7 Days | +/- 7 Days | +/- 2 Weeks | +/- 7 Days | +/- 4  Weeks |
| ADT^A^ |  | X |  |  |  |  |  |  |  |
| FT^B^ |  |  |  | X |  |  |  |  |  |
| Consent | X |  |  |  |  |  |  |  |  |
| Demographics | X |  |  |  |  |  |  |  |  |
| Med hx | X |  |  |  |  |  |  |  |  |
| Con meds^C^ | X | X------------------------------------X^C^ | | | |  |  |  |  |
| AEs^C^ | X | X-------------------------------------X^C^ | | | |  |  |  |  |
| Full PE | X |  |  |  |  |  |  |  |  |
| Focused PE^D^ |  |  |  |  | X | X | X | X | X |
| Vital signs^E^ | X |  |  |  |  |  |  |  |  |
| ECOG | X |  |  |  | X | X |  |  |  |
| I-PSS, SHIM^F^ | X |  |  |  | X | X | X | X | X |
| EPIC-26^F^ | X |  |  |  |  | X | X |  | X |
| PSA, Testosterone ^G^ | X^G^ |  | X |  |  | X | X | X | X |
| CBC/CMP/^H^ | X |  |  |  |  |  |  |  |  |
| mpMRI |  |  | X |  |  |  |  |  | X |
| MRI-TB |  |  |  |  |  |  |  |  | X |
| Correlative labs^I^ | X |  |  |  | X |  |  |  |  |
| Correlative bx^I^ |  |  |  | X |  |  | X |  | X |
| LTFU data^J^ |  |  |  |  | X | X | X |  | X |
| Remove FC^K^ |  |  |  | X^K^ |  |  |  |  |  |

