**Calendar Footnotes**

1. ADT therapy will consist of any generic luteinizing hormone-releasing hormone agonist which will provide 3-months of treatment (e.g.,.
2. Focal therapy to be completed within 8- to 12-weeks of the initiation of ADT but after the completion of the 8-week mpMRI to allow for it to be used in FT planning.
3. Both adverse events (AEs) and serious AEs and any conmeds to be collected from the time of consent and continuously throughout the study until 30-days after the FT or as indicated in Section 14 of this protocol.
4. Focused abdominal and pelvic genitourinary exam. To be completed once a subject has entered into post-FT follow-up and only as clinically indicated.
5. Vital signs should include: temperature, pulse, respiratory rate, height, weight and blood pressure.
6. Health related quality of life measures including EPIC-26, the I-PSS and the SHIM must be collected at screening. If any of these are not done at screening then these may be completed at Visit 2.
7. PSA collected at “baseline” is defined within eligibility for this protocol. PSA and testosterone value is collected at 3-, 6-, 9- and 12-months post-FT.
8. Screening CBC & CMP, and testosterone must be collected and reviewed for safety within 15-days prior to the initial dose of ADT. Collection at other timepoints only if clinically indicated.
9. A single purple top EDTA tube of 3mL of whole blood to be collected after eligibility is confirmed for banking for future germline testing and at 6-weeks after FT. At the time of FT two 18-gauge biopsy cores will be collected from the target area(s) and one each from peritumoral and untreated prostate. At the time of 6-month MRI-TB two 18-gauge biopsy cores will be collected from the ablated area(s) and one each from periablation zone and untreated prostate.
10. Long term follow-up (LTFU) data collection to begin at 6-weeks after FT and includes collection of any recurrence, re-treatment, survival, and other relevant post-surgical data through 1-year post-FT.
11. FT foley catheter to be removed 1 weeks after FT +/- 3 days.

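### The two adverse event collection windows conflict: one closes before focal therapy takes place, the other 30 days after it, although safety of the combination is a primary endpoint

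*Protocol*

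**What the plan says.** Study Design/Endpoints lists safety of androgen deprivation therapy (ADT) plus FT as a primary endpoint, using the "CTCAE v.5 classification to quantify and characterize the incidence of AEs". No time horizon is attached.

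Two places set the end of adverse event (AE) and serious adverse event (SAE) collection:

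- Section 14, Adverse Event (AE) Definitions: "Subjects will be followed for AEs/SAEs for 30 days after their last dose of study drugs".
- Calendar Footnotes, footnote 3: from consent, "continuously throughout the study until 30-days after the FT or as indicated in Section 14 of this protocol". The AE row of the Study Calendar matches the first half of this. It runs to the 30-day visit after FT and is blank at 3, 6, 9 and 12 months.

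The treatment sequence is fixed elsewhere. ADT is a "3-month injection once at baseline for a total of 3-months of treatment", and the calendar marks it at Visit 2 only. On FT, the treatment plan says "Within 8- to 12-weeks of initiation of ADT, FT will be performed" and also that "each participant will complete at least 8-weeks of neoadjuvant treatment prior to FT". The calendar places FT at "8-12 wks from V2", within 7 days either way.

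**The concern.** A safety endpoint for a combination has to count events after both components have been given. The Section 14 rule is tied to the drug, and the drug is given once, weeks before the procedure. The analysis populations make the mismatch sharper. The safety analysis set consists of men who received ADT and FT, so every man enters it through a procedure performed after his Section 14 window has closed.

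The calendar rule does include FT but stops 30 days later. The planned peri-operative table nevertheless reports stricture and recto-urethral fistula with no time limit, and the protocol allows one redo FT during follow-up.

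Safety data are to be analysed as available, without imputation. An event that was never collected is therefore counted as absent, and the error runs in one direction, towards a lower complication rate. In a multi-institutional trial, sites may also apply different rules, which would make counts differ between sites for reasons unrelated to safety.

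**Working it through.** The protocol gives no figure of its own to reproduce here. The check is day arithmetic, with day 0 as the single ADT injection.

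**Inputs**
- Last (and only) study-drug dose: day 0 (Pharmacological Treatments; Study Calendar).
- FT: 8 × 7 = day 56 to 12 × 7 = day 84. With the 7-day visit window, 56 − 7 = day 49 to 84 + 7 = day 91.
- Follow-up after FT: 12 months, taken as 365 days.

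**Section 14 rule**
- Window closes: 0 + 30 = day 30.
- Gap before FT: 56 − 30 = 26 days to 84 − 30 = 54 days. With visit windows, 49 − 30 = 19 to 91 − 30 = 61 days.
- Days after FT covered: 0 of 365. This holds even at the earliest FT date allowed.

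**Calendar rule**
- Window closes: 56 + 30 = day 86 to 84 + 30 = day 114.
- Days after FT covered: 30 of 365 = 8.2%. If the 30-day visit falls 7 days late, 37 of 365 = 10.1%.
- Days without scheduled AE collection: 365 − 30 = 335.

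**Sensitivity to the meaning of last dose.** Suppose it meant the end of the depot's effect, assumed to be day 91. Section 14 would then close on 91 + 30 = day 121. That is 121 − 84 = 37 to 121 − 56 = 65 days after FT, or 10% to 18% of the year. This would be a third window that agrees with neither of the other two.

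**Which rule governs.** The Adverse Events paragraph under Other Research Activity Specifications sends sites to the calendar for timing and to Section 14 for assessment, recording and reporting. Footnote 3 of the calendar sends them to Section 14 again. Nothing says which prevails.

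**What else is captured after day 30 post-FT**

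| Provision | What it adds | Why it is not scheduled AE collection |
| --- | --- | --- |
| Section 14: open interview at each evaluation; AEs tracked to resolution on study | May elicit new events; completes open ones | The same subsection sets the 30-day limit; the calendar marks no AE assessment |
| Medical History: subjects asked at each visit, CTCAE grading required | New conditions and admissions | Recorded as history; the calendar marks it at screening only |
| Hospitalization and SAE reporting rules | On-study admissions and other serious events | Do not reach non-serious events managed without admission |
| Long-term follow-up data and quality-of-life questionnaires | Unspecified post-surgical data; urinary, bowel and sexual scores | Not graded AEs, and not what the endpoint counts |

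**Redo FT.** The ablation-template principles and the post-FT surveillance section both allow a second FT. A 30-day window counted from the first FT would miss its toxicity. The surveillance section gives re-treated men the same visits as after the first treatment, but ends study follow-up 12 months after the first FT.

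**The case against.** The best reply is that the calendar is the working schedule. Its AE row runs to a visit labelled as end of treatment and placed 30 days after FT, and the Adverse Events paragraph directs sites there. A site that follows it will record peri-ablation events. The Section 14 sentence comes straight after text on patients removed from the study and can be read as a minimum follow-up after drug. It can also be argued that the endpoint names no time horizon, so a 30-day post-procedure window does not contradict it and longer collection is a design preference.

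Much of this stands. A reader might infer that the trial will record no ablation toxicity, that all later toxicity will be lost, or that a count of zero late events would carry no information about the rest of the year. The protocol does not support any of these. The calendar covers the first 30 days after FT, and the interviews, medical history, SAE rules, long-term follow-up and questionnaires give partial capture later. The 8.2% is a share of calendar time, not of toxicity.

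Two things remain. Footnote 3 does not make the calendar prevail, because it defers to the conflicting rule. And none of the later provisions is scheduled, CTCAE-graded collection of new AEs, which is what the endpoint counts.

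**Conclusion.** The concern holds as an inconsistency in the data window for a primary endpoint, together with thin late coverage under the more generous rule. The Section 14 wording covers 0 of 365 days after FT and the calendar covers about 30. This rests on the single baseline injection, FT at weeks 8 to 12, and a literal reading of last dose; reading it as the end of depot effect only produces a third window.

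Late AE incidence is likely to be under-counted. The size of the bias cannot be stated, because the protocol gives no expected rate or timing of late events and the partial capture routes will recover some of them. The first part, the conflict between the rules, has to be resolved. The second, how long to collect, is a choice, but the reported safety claim must match the window chosen.

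**What to change.** Reconcile the Section 14 sentence, the calendar AE row and footnote 3 into one rule, and remove the deferral to Section 14. The rule should name FT explicitly: all AEs and SAEs from consent through at least 30 days after the last FT, first or redo. Then add CTCAE-graded recording of SAEs and of genitourinary, rectal and treatment-related AEs at the existing 3-, 6-, 9- and 12-month visits, and state the period that the stricture and fistula rows cover.

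If the sponsor prefers not to extend the window, the safety endpoint should be described and reported as safety to 30 days after FT only.

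The cost is an AE form at four visits that already exist, and an amendment. One detail needs a decision: a redo prompted by the 12-month biopsy would place its 30 days beyond the present end of study follow-up, so the rule must say whether AE collection continues for those men.
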